#### 2.8.4. Sample-Size Justification

Total enrollment will target 700 patients (350 by group). The trial is designed with >80% power to detect a difference of 2 days alive and off ventilation at day 28 (primary outcome of VFD28), with standard deviation of 8 [43,44] and two-sided type I error of 5%. For this calculation, we assumed the variability of VFD28 would follow the properties of ROSE [21], the Esophageal Pressure-guided Ventilation-2 (EPVent-2) trial [45], and a pilot study of inhaled sevoflurane in ARDS [14], with 28 day mortality around 30–35% [21,24,45].

## 3. Discussion

The SESAR trial was designed to investigate the efficacy and safety of inhaled sevoflurane compared with intravenous propofol in patients with ARDS. The trial uses prognostic enrichment by enrolling the most severe patients (i.e., with a PaO_2_/FiO_2_ <150 mmHg) and, therefore, a greater probability of experiencing worse clinical outcomes [46,47]. The protocol implies strict adherence to evidence-based guidelines for analgesia-sedation and ventilation in ARDS, including recommendations on the ABCDEF bundle for ICU liberation and avoidance of benzodiazepines [48,49], and on lung-protective ventilation with low tidal volume and PEEP, prone position, and conservative fluid therapy unless the patient is in shock [27,50,51]. Based on the recent Severe ARDS: Generating Evidence (SAGE) Study, a multicenter, observational cohort study of 2466 mechanically ventilated adult patients with ARDS and PaO_2_/FiO_2_ < 150 mmHg on PEEP > 5 cmH_2_O in the United States, only adherence to early lung protective ventilation was associated with lower mortality [52]. The SESAR protocol stresses the use of lower tidal volumes (4 to 8 mL/kg PBW), and data monitoring has been developed to reveal whether higher tidal volumes are applied.

Early deep sedation will be targeted and associated with a systematic neuromuscular blockade in the trial, which is debatable [18,20,21]. However, this overall trial strategy has been chosen to avoid the substantial center-to-center variability that exists in ARDS management, while ensuring implementation of underused evidence-based interventions such as lung-protective ventilation and prone position [52]. In both study arms, deep sedation followed by a neuromuscular blockade will be initiated to reduce the risk of patient–ventilator asynchrony and patient self-inflicted lung injury [53]. This initial strategy will be switched for a lighter or no-sedation strategy as soon as oxygenation improves, thus better personalizing sedation and the neuromuscular blockade [24]. After this period, priority will be given to respiratory drive control and patient–ventilator synchrony to avoid the unnecessary use of medications such as sedatives, opioids, and neuromuscular blocking agents (paralysis over 48 h after randomization will be considered a rescue therapy) [18]. PEEP will be individually titrated based on plateau pressure, regardless of its effect on oxygenation in contrast to the PEEP/FiO_2_ scales used in other studies [32,54].

The trial will evaluate VFD28 as a primary, patient-centered outcome measure that represents the number of days alive and free of invasive mechanical ventilation calculated over 28 days. This endpoint, designed to assign benefit to early liberation from mechanical ventilation while considering death as a competitive risk, has been approved by the US Food and Drug Administration for licensing and is a clinically relevant outcome for phase III ARDS trials enrolling more than 500 patients [46]. Longer-term outcomes will also be evaluated in the trial, as there is an increased recognition of the significant long-term consequences of ARDS [55,56].

The precise pathways to lung-protective effects of sevoflurane, as observed in preclinical models and a pilot clinical trial [3,11,14], are largely unknown. The most commonly proposed mechanism is through the preservation of alveolar-epithelial integrity [57] and a reduction in pro-inflammatory cytokine release [6,7,9,10,14,58]. The SESAR trial includes the rigorous and sequential collection of plasma, alveolar, and urine samples that will be used to better characterize the effects of sevoflurane on major pathophysiological features of ARDS, in addition to assess renal laboratory markers and levels of sevoflurane metabolites. The results will also inform whether specific ARDS phenotypes might better benefit from inhaled sevoflurane, and which clinico-biological features and/or natural histories may be capable of predicting therapeutic response, and not just prognosis [59,60,61,62].

Although routinely used in some countries, inhaled sedation practice may largely vary among ICUs [2,4]. Volatile anesthetics use for ICU sedation requires specific training and specialized equipment, and some specific settings have also been suggested to increase viral protection in COVID-19 patients while ensuring safety to healthcare workers [63]. Sevoflurane is a well-known trigger to malignant hyperthermia in genetically predisposed patients, a syndrome that requires early intervention with the immediate change of the ventilator circuit and dantrolene infusion. However, this condition remains rare (1/50,000–100,000) in comparison to propofol infusion syndrome, which affects up to 1% of ICU patients [64]. The trial includes the remote and on-site training of all clinical teams to ensure strict adherence to the intended use and safety of inhaled sedation. Because we lack a cost-effectiveness analysis that takes into account any beneficial clinical outcomes such as faster awakening, extubation times, and lengths of ICU stay [65,66], the trial will also explore cost-effectiveness of sevoflurane compared with current practices.

SESAR is a randomized multicenter trial of inhaled sevoflurane in patients with ARDS. If the trial results demonstrate that sevoflurane increases VFD28 (primary endpoint) or 90 day survival (key secondary endpoint), compared with the current practice of intravenous propofol, increased use of inhaled ICU sedation should be considered. Better understanding of how sevoflurane may target major biological features of lung alveolar injury and their contributions to heterogeneity of the treatment effect will enhance the interpretation of trial results and inform future efforts in the early treatment of ARDS.

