### 2.4. Randomization

All patients were randomized online (CSOnline, Clinsight) by local investigators within 24 h of meeting inclusion criteria on a 1:1 ratio for the two study arms. The randomization sequence was generated by minimization and stratified by the study center, the degree of ARDS severity (PaO_2_/FiO_2_ < 100 mmHg), the suspicion or presence of COVID-19, and the presence of shock (defined as intravenous infusion of vasoactive drugs) at enrollment.

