#### 2.8.3. Statistical Considerations

The statistical analysis plan is provided in Supplementary Material File S7. A two-sided *p* value < 0.05 will be considered for significance of all analyses, except for interim analysis. The primary analysis will be performed using an intention-to-treat (ITT) principle. Then, we will perform per-protocol and subgroup analyses on the primary and secondary outcomes (Table 3). The primary endpoint (VFD28) will be analyzed using a mixture of generalized gamma distributions to concatenate the overall frequency and distribution of the times [42]. Multivariable adjustments will be performed in (1) a first model including only the randomization-stratification variables and center as random-effect; (2) a second model with covariates from the first model and covariates with clinically relevant relationships with the outcome and significant in univariate analyses (*p* < 0.10). The key secondary outcome of day 90 survival will be evaluated using the Kaplan–Meier approach and compared using the log-rank test (univariate analysis); multivariable adjustments will be conducted using the same two models described above. Because of the potential for type I error due to multiple comparisons, findings for analyses of other secondary endpoints will be interpreted as exploratory.

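### The practice conclusion may rest on VFD28 or 90-day survival, each tested at 0.05 with no stated order, so its error is about 8% two-sided, or about 4% for a false benefit claim

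*Protocol article*

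**What the plan says.** All references are to the protocol article.

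- **Ranking.** Sections 2.7.1 to 2.7.4 and Table 2 name VFD28 as the only primary outcome and 90-day survival as the only key secondary outcome. Mortality at days 7, 14 and 28 and hospital mortality at day 28 form the other secondary outcomes. Exploratory outcomes follow.
- **Significance level.** Section 2.8.3 sets one threshold throughout: a two-sided p "value < 0.05 will be considered for significance of all analyses, except for interim analysis".
- **Multiplicity.** The same section acknowledges the risk from multiple comparisons, but its remedy is that "findings for analyses of other secondary endpoints will be interpreted as exploratory". As 90-day survival is the key secondary outcome, it falls outside that label. It has its own log-rank test, with no condition on the VFD28 result.
- **Conclusion.** Section 3 (Discussion) reads "If the trial results demonstrate that sevoflurane increases VFD28 (primary endpoint) or 90 day survival (key secondary endpoint") against propofol, and continues that greater use of inhaled sedation in intensive care should then be considered.
- **Sample size.** Section 2.8.4 is built on VFD28 alone, with a "two-sided type I error of 5"%.
- **Analysis plan.** Section 2.8.3 refers to File S7, which is not shown.

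**The concern.** The word *or* in the Discussion gives the practice conclusion two chances. Section 2.8.3 gives each chance the full 0.05, and its exploratory label stops short of the second one. Read together, these passages allow a trial that misses its primary endpoint to support wider use of inhaled sedation on 90-day survival alone. The 5% type I error in the sample-size section is then the error of the VFD28 test, not of the conclusion that the article intends to draw.

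This does not depend on the unseen analysis plan. If File S7 sets a testing order, the Discussion sentence contradicts it. If it does not, the either-endpoint conclusion is not held at 5%. In both cases the sentence needs changing.

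**Working it through.** **1. Reproduce the plan's own figure.** Inputs from sections 2.4 and 2.8.4: "Total enrollment will target 700 patients (350 by group"), allocated "on a 1:1 ratio for the two study arms"; "The trial is designed with >80% power to detect a difference of 2 days alive and off ventilation at day 28"; "with standard deviation of 8"; two-sided alpha 0.05.

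Standard error = 8 × √(2/350) = 0.6047. Expected z = 2 / 0.6047 = 3.307. Power = Φ(3.307 − 1.960) = Φ(1.347) = 91.1%. This agrees with the stated inequality (80% needs 252 per group and 90% needs 337). It concerns VFD28 only.

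**2. Upper reference: independent tests.**
- Two-sided, at least one rejection: 1 − (1 − 0.05)² = 0.0975.
- In favour of sevoflurane only: 1 − (1 − 0.025)² = 0.0494.

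**3. Allow for correlation.** Section 2.7.1 scores VFD28 as zero for death before day 28, and those deaths also count in 90-day survival. The two test statistics are therefore positively correlated. With both null hypotheses true and (Z1, Z2) bivariate normal with correlation ρ:
- two-sided error = 1 − P(|Z1| < 1.96 and |Z2| < 1.96)
- benefit-direction error = 1 − P(Z1 < 1.96 and Z2 < 1.96)

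| ρ (assumed) | Two-sided | Benefit direction |
|---|---|---|
| 0 | 0.0975 | 0.0494 |
| 0.5 | 0.0907 | 0.0454 |
| 0.6 | 0.0875 | 0.0438 |
| 0.7 | 0.0835 | 0.0417 |
| 0.8 | 0.0781 | 0.0390 |
| 0.9 | 0.0704 | 0.0352 |

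**4. What correlation is plausible?** The documents do not give it, so it was simulated under the null with 350 per group and 4,000 trials per scenario. Mortality at 28 days was 30% or 35%, the range in section 2.8.4. The rest is assumption: 90-day mortality of 35% to 50%; early death times exponential with mean 10 days, capped at day 28; late deaths spread evenly over days 29 to 90; ventilation time gamma with shape 1.5 and scale 8 days; VFD28 set to zero in 60% of patients who die after day 28. VFD28 was compared by a z-test on means, in place of the planned generalized-gamma mixture. No interim look was modelled.

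| Mortality at 28 / 90 days | Correlation | Either test, two-sided | Either test, benefit |
|---|---|---|---|
| 30% / 35% | 0.73 | 0.0825 | 0.0403 |
| 30% / 45% | 0.71 | 0.0850 | 0.0475 |
| 35% / 40% | 0.76 | 0.0853 | 0.0428 |
| 35% / 50% | 0.73 | 0.0750 | 0.0370 |

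The Monte Carlo standard error is about √(0.08 × 0.92 / 4,000) = 0.004 for the two-sided column and √(0.04 × 0.96 / 4,000) = 0.003 for the benefit column. In the 0.0475 run, the two single tests themselves rejected in 2.8% and 2.85% of trials rather than 2.5%, so part of its excess is sampling noise. The simulated standard deviation of VFD28 was about 10 days, not 8. The simulation therefore serves only to place the correlation at roughly 0.7 to 0.76. There the formula gives about 8.0% to 8.3% two-sided and about 4.0% to 4.1% for benefit.

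**5. Ratio.** 0.080 / 0.05 = 1.6 and 0.083 / 0.05 = 1.7. In the benefit direction, 0.040 / 0.025 = 1.6.

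**6. After the change.** If survival is tested only after VFD28 is significant, a false claim on both true nulls requires a false VFD28 result first. The error is then at most 0.05 two-sided, or 0.025 for benefit. The VFD28 test is untouched, so the 91.1% of step 1 stands.

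**The case against.** The strongest reply is that the article sets no success rule of this kind. The sentence comes at the end of a Discussion, its consequence is only that wider use be considered, and the design has one primary endpoint to which sample size and alpha are tied. The endpoints are ranked, a multiplicity caveat is given, and nowhere is 90-day survival called confirmatory. Testing order is commonly left to the analysis plan, which exists but is not shown.

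Much of this stands, and it rules out several stronger readings that a reader might take from these passages:

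- *That the error nearly doubles.* The 9.75% figure needs independent tests, which the definition of VFD28 excludes. The plausible factor is 1.6 to 1.7.
- *That the trial will be declared a success on either endpoint.* The text states a practice conclusion, not a formal success criterion.
- *That there is no hierarchy.* The outcomes are ranked. What the article does not state is a testing order, and File S7 may contain one.
- *That the primary test is compromised.* Its alpha is unaffected by this sentence.
- *That 8% is the risk of a false recommendation.* The sentence concerns benefit only. The two-sided figure also counts false signals of harm, so about 4% against 2.5% is the closer measure.
- *That the interim look adds a known further amount.* Section 2.8.2 does provide group sequential boundaries, and no extra inflation can be derived from the article.

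What does not stand is that ranking alone answers the point. The Discussion uses both rank labels and still joins the endpoints with *or*, and section 2.8.3 leaves the key secondary outcome outside its exploratory caveat. That is a matter of what the article states, not of what it leaves out.

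**Conclusion.** The point holds in a limited form. As written, the practice conclusion can rest on either endpoint at the full 0.05. Its error is about 8% two-sided, with a range of 7.0% to 9.1% for assumed correlations of 0.9 to 0.5. For a false claim of benefit it is about 4% (3.5% to 4.5% over the same range) instead of 2.5%.

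These figures assume that neither endpoint is affected by treatment, that each test holds its nominal level, and that the statistics are jointly normal. The choice of correlation near 0.7 rests on the simulation assumptions listed above and on a means test in place of the planned mixture model.

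The inconsistency should be put right, but it ranks below a must-fix. The primary analysis is sound on this point, and a testing order may already exist in File S7.

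**What to change.** 1. State in the analysis plan that 90-day survival is tested confirmatorily at the full level only if VFD28 is significant at its final boundary, and is otherwise supportive and descriptive. If File S7 already contains such an order, nothing needs adding there.
2. Reword the conclusion, in the protocol and in the eventual report, so that it rests on VFD28, with survival as a supporting claim that depends on it.

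The cost is one sentence and one change of wording. VFD28 keeps its full alpha and its power. The loss is that survival could not be claimed alone if VFD28 fails, but the sample-size section never covered a stand-alone survival claim.

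Splitting alpha at 0.025 each would also cap the error at 0.05 and would keep that claim open, at the expense of the primary: power for VFD28 becomes Φ(3.307 − 2.241) = Φ(1.066) ≈ 86% instead of 91.1%. The fixed sequence is the simpler choice and matches the ranking already in the article.

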## Figures and Tables

**Figure 1 jcm-11-02796-f001:**
[figure not shown]
CONSORT diagram of the SESAR trial. * Because, in emergency situations, sedation and ventilation must be initiated as early as possible, the study protocol provides for a waiver of informed consent from the patient. The consent from the patient’s next of kin will therefore be sought actively during the 24 h enrollment time window. In case the patient’s next of kin cannot be reached in a timely manner, the investigator will decide to include the patient in the study using an emergent consent procedure. Deferred informed consent will be obtained from participants for potential continuation of the research.

**Figure 2 jcm-11-02796-f002:**
[figure not shown]
Summary of interventions within the SESAR trial. Definition of abbreviations: SESAR = sevoflurane for sedation in ARDS; ARDS = acute respiratory distress syndrome; RASS = Richmond agitation-sedation scale; BPS = behavioral pain scale; PBW = predicted body weight; PEEP = positive end-expiratory pressure; Pplat = inspiratory plateau pressure.

**Table 1 jcm-11-02796-t001:** Inclusion and exclusion criteria.

Inclusion criteria	Age ≥ 18 years Presence for ≤24 h of all the following conditions, within one week of a clinical insult or new or worsening respiratory symptoms: a. PaO_2_/FiO_2_ < 150 mmHg with positive end-expiratory pressure (PEEP) ≥8 cmH_2_O ^i,ii,iii^ or, if arterial blood gas is not available, SpO_2_/FiO_2_ ratio that is equivalent to a PaO_2_/FiO_2_ <150 mmHg with PEEP ≥ 8 cmH_2_O, and a confirmatory SpO_2_/FiO_2_ ratio between 1–6 h after the initial SpO_2_/FiO_2_ ratio determination ^iii,iv^ b. Bilateral opacities not fully explained by effusions, lobar/lung collapse, or nodules c. Respiratory failure not fully explained by cardiac failure or fluid overload; needs objective assessment (e.g., echocardiography) to exclude hydrostatic edema if no risk factor is present d. The 24 h enrollment time window begins when criteria a–c are met.
Exclusion criteria	Absence of affiliation to the French *Sécurité Sociale* Patient under a tutelage measure or placed under judicial protection Continuous sedation with inhaled sevoflurane at enrollment Known pregnancy Currently receiving ECMO therapy Chronic respiratory failure defined as PaCO_2_ >60 mmHg in the outpatient setting Home mechanical ventilation (non-invasive ventilation or via tracheotomy) except for CPAP/BIPAP used solely for sleep-disordered breathing Body mass index >40 kg/m^2^ Chronic liver disease defined as a Child–Pugh score of 12–15 Expected duration of mechanical ventilation <48 h Moribund patient, i.e., not expected to survive 24 h despite intensive care Burns > 70% total body surface Previous hypersensitivity or anaphylactic reaction to sevoflurane or cisatracurium Medical history of malignant hyperthermia Long QT syndrome at risk of arrhythmic events Medical history of liver disease attributed to previous exposure to a halogenated agent (including sevoflurane) Known hypersensitivity to propofol or any of its components Known allergy to eggs, egg products, soybeans, and soy products Suspected or proven intracranial hypertension Tidal volume of 6 mL/kg PBW below 200 mL (as recommended by the manufacturer for the use of the Sedaconda ACD-S (Sedana Medical, Danderyd, Sweden) Enrollment in another interventional ARDS trial with direct impact on sedation and mechanical ventilation Endotracheal ventilation for greater than 120 h (5 days) Persistent bronchopleural fistula despite chest tube drainage PaO_2_/FiO_2_ (if available) >200 mmHg after meeting inclusion criteria and before randomization.

*Definition of abbreviations:* PaO_2_ = partial pressure of arterial oxygen; FiO_2_ = fraction of inspired oxygen; PEEP = positive end-expiratory pressure; ECMO = extracorporeal membrane oxygenation; PaCO_2_ = partial pressure of arterial carbon dioxide; CPAP = continuous positive airway pressure; BIPAP = bi-level positive airway pressure; PBW = predicted body weight; ARDS = acute respiratory distress syndrome. i. If altitude > 1000 m, then PaO_2_/FiO_2_ < 150 x (PB/760). ii. These inclusion criteria ensure a non-transient, established hypoxia that persists despite elevated PEEP and time. Initial, post-intubation, PEEP is typically <8 cmH_2_O. iii. The qualifying PaO_2_/FiO_2_ or the SpO_2_/FiO_2_ must be from intubated patients receiving at least 8 cmH_2_O PEEP. iv. When hypoxia is documented using pulse oximetry, a confirmatory SpO_2_/FiO_2_ ratio is required to further establish persistent hypoxia. Qualifying SpO_2_/FiO_2_ must use SpO_2_ values less than or equal to 96% Qualifying SpO_2_ must be measured at least 10 min after any change to FiO_2_. The first qualifying SpO_2_/FiO_2_ (not the confirmatory SpO_2_/FiO_2_) is used to determine the 24 h enrollment time window. See Supplementary Material File S1 for details on imputations of PaO_2_/FiO_2_ based on combinations of SpO_2_ and FiO_2_.

**Table 2 jcm-11-02796-t002:** SESAR trial outcome measures.

Primary outcome	Ventilator-free days through day 28 (VFD28), as defined as the number of days alive and off the ventilator at 28 days, thereby considering death as a competing event *
Key secondary outcome	90 day survival (assessed on study day 91)
Secondary outcomes	All-location, all-cause 28 day mortality (assessed on study day 29) All-cause hospital 28 day mortality (assessed on study day 29) All-location, all-cause 14 day mortality (assessed on study day 15) All-location, all-cause 7 day mortality (assessed on study day 8)
Exploratory outcomes	Ventilator-free days through day 14 (VFD14) Ventilator-free days through day 7 (VFD7) Organ failure-free days through day 7 ** ICU-free days through day 28 Hospital-free days through day 28 Physiological measures to include: o Changes in oxygenation index, PaO_2_/FiO_2_, PaCO_2_, and arterial pH from day 1 to day 7 (defined as continuous time-dependent variables) o Changes in the level of PEEP (and static auto-PEEP in patients under controlled ventilation), inspiratory plateau pressure and static compliance of the respiratory system, and in ventilatory ratio^#^ from day 1 to day 7 (defined as a continuous time-dependent variable) Use of rescue procedures for refractory hypoxemia through day 28: nitric oxide, epoprostenol sodium, high frequency ventilation, ECMO, and neuromuscular blockade use after 48 h from randomization. ICU-acquired delirium: CAM-ICU assessed daily from study entry to study day 7, death or ICU discharge, whichever comes first. Long-term outcome assessments at 3 and 12 months: o Disability: Katz Activities of Daily Living o Health-Related Quality of Life: Short Form-36 o Pain-interference: 1 standard item o Post-traumatic Stress-like Symptoms: Post-Traumatic Stress Symptoms-14, Hospital Anxiety and Depression Scale o Cognitive function: Alzheimer’s Disease 8 o Subsequent return to work, hospital and ED use, and location of residence Healthcare-related costs during ICU stay and hospital stay
Exploratory biological outcomes	Change in plasma biomarkers of IL-8, sTNFr1, bicarbonates (hyperinflammatory ARDS phenotype), IL-6 (VILI), ANG-2 (endothelial activation), and sRAGE (alveolar epithelial injury) (defined as continuous time-dependent variables) ^§^ Change in urine biomarkers of TIMP-2 and IGFBP-7 (acute kidney injury) ^§^ Change in plasma total fluoride and hexafluoroisopropanol (sevoflurane metabolism) Genetic analysis: DNA and RNA at baseline and 48 h Change in total protein within undiluted pulmonary edema fluid at baseline and 24 h (alveolar fluid clearance) ^£^ Biomarker measurements in the fluid from the HME filter (control group) and Sedaconda ACD-S device (intervention group) at baseline and 24 h ^$^ Biomarker measurements in the BAL fluid within 48 h from study entry and between day 4 and day 6 ^€^
Safety outcomes	Changes in hemodynamic measures (mean arterial pressure, dose of infused norepinephrine or other vasopressor, serum lactate level) and in KDIGO criteria for acute kidney injury from day 1 to day 7 (defined as continuous time-dependent variables) Supraventricular tachycardia or new onset atrial fibrillation through day 7 Severe hypercapnic acidosis with arterial arterial pH < 7.15 ^%^ through day 7 (Sedaconda ACD-S device) Development of malignant hyperthermia through day 7 (sevoflurane) Development of propofol-related infusion syndrome through day 7 (propofol) Development of pneumothorax or bronchopleural fistula persistent despite drainage, through day 7

*Definition of abbreviations:* SESAR = sevoflurane for sedation in acute respiratory distress syndrome; VFD = ventilator-free days; ICU = intensive care unit; PEEP = positive end-expiratory pressure; ECMO = extracorporeal membrane oxygenation; CAM-ICU = confusion assessment method for the ICU; ED = emergency department; IL-8 = interleukin 8; sTNFR1 = soluble tumor necrosis factor receptor 1; IL-6 = interleukin 6; ANG-2 = angiopoietin 2; sRAGE = soluble receptor for advanced glycation end-products; TIMP-2 = tissue inhibitor of metalloproteinase 2; IGFBP-7 = insulin-like growth factor binding protein 7; DNA = deoxyribonucleic acid; RNA = ribonucleic acid; HME = heat moisture exchanger; BAL = bronchoalveolar lavage; KDIGO = kidney disease improving global outcomes. * Ventilator-free days through day 28 are defined as the number of days from the time of initiating unassisted breathing to day 28 after randomization, assuming survival for at least two consecutive calendar days after initiating unassisted breathing and continued unassisted breathing to day 28. If a patient returns to assisted breathing and subsequently achieves unassisted breathing to day 28, VFDs will be counted from the end of the last period of assisted breathing to day 28. A period of assisted breathing lasting less than 24 h and for the purpose of a surgical procedure will not count against the VFD calculation. If a patient was receiving assisted breathing at day 27 or dies prior to day 28, VFDs will be zero. Patients transferred to another hospital or other healthcare facility will be followed to day 28 to assess this endpoint. ** Organ failure is defined as present on any date when the most abnormal vital signs or clinically available lab value meets the definition of clinically significant organ failure according to SOFA scores. Patients will be followed for the development of organ failures to death, hospital discharge, or study day 7, whichever comes first. Each day a patient is alive and free of a given organ failure will be scored as a failure-free day. Any day that a patient is alive and free of all organ failures will represent days alive and free of all organ failure. # Ventilatory ratio = [minute ventilation (mL/min) × PaCO_2_ (mmHg)]/[predicted body weight × 100 × 37.5] ^§^ Plasma and urine samples will be collected from indwelling catheters (when available) at study entry and on days 1, 2, 4, 6, and 14 or ICU discharge (whichever occurs first). ^£^ In 50 patients from each group. ^$^ In 30 patients from each group. ^€^ In a total of 25 patients. ^%^ In the absence of metabolic acidosis and despite further tidal volume and/or respiratory rate increase, as described in the protocol.

**Table 3 jcm-11-02796-t003:** SESAR trial populations for primary, key secondary, secondary, and subgroup analyses.

Intention-to-treat population	All randomized patients except those who withdraw their consent for the use of data.
Per-protocol population #1	All randomized patients except patients having one or more major protocol violations defined as: Inhaled sevoflurane not administered in patients randomly allocated to the intervention arm *OR* 2. Inhaled sevoflurane not administered during the whole duration of sedation (within a maximum of 7 days from randomization) in patients randomly allocated to the intervention arm *OR* 3. Monitoring revealed that a tidal volume higher than 8 mL/kg PBW was applied *OR* 4. Monitoring revealed that one or more inclusion or exclusion criteria were violated *OR* 5. Patients withdrawn from the protocol because the patient would have withdrawn consent
Per-protocol population #2	All randomized patients except patients having one or more major protocol violations defined as: Inhaled sevoflurane was not administered in patients randomly allocated to the intervention arm *OR* 2. Inhaled sevoflurane was not administered during the whole duration of sedation (within a maximum of 7 days from randomization) in patients randomly allocated to the intervention arm
Subgroup populations	Patients with shock (defined as the need for intravenous vasopressor infusion to maintain arterial pressure) at randomization Patients with pre-randomization PaO_2_/FiO_2_ <100 mmHg Pre-randomization presence vs. absence of suspected COVID-19 Patients with hypoinflammatory versus hyperinflammatory phenotypes at randomization Patients with higher versus lower degrees of lung epithelial injury at randomization, as assessed by plasma sRAGE (thresholds to be determined according to univariate analyses and clinical relevance) Patients with higher versus lower degrees of lung endothelial injury at randomization, as assessed by baseline plasma ANG-2 (thresholds to be determined according to univariate analyses and clinical relevance) Patients with focal versus nonfocal ARDS at baseline, as assessed by lung CT-scan, chest radiograph, or bedside lung ultrasound (if available) Patients treated with lower (5–10 cmH_2_O), moderate (11–15 cmH_2_O), or higher (>15 cmH_2_O) levels of PEEP during the first 3 days after enrollment

Definition of abbreviations: SESAR = sevoflurane for sedation in acute respiratory distress syndrome; PBW = predicted body weight; sRAGE = soluble receptor for advanced glycation end-products; ANG-2 = angiopoietin 2; CT = computerized tomography; PEEP = positive end-expiratory pressure; COVID-19 = coronavirus disease 2019.
